### Monitoring

#### Steering Group

The CHOICE steering group (SG) meets every 4 months and comprises the CHOICE chief investigator; project manager (PM); 2 patients; coordinators of 2 other cochlear implant centers; the lead of the independent evaluation team; and senior representatives from the NHS Specialist Commissioning, The Ear Foundation, and the National Cochlear Implant Users Association. The purpose is to advise and guide the project by reflecting differing stakeholder needs to maximize success and ensure the long**-**term sustainability of the project. The SG acts as a sounding board for the project, particularly in relation to key project risks (including time, cost, quality, commercial, legal, and ethical risks). The SG also deals with safety monitoring, adverse events, data monitoring, deviations from and breaches of protocol, and major project changes.

#### Evaluation Advisory Group

The evaluation advisory group (EAG) is a requirement of the project funder and its remit relates to the independent evaluation of CHOICE. The EAG meets every 3 months and comprises the Wessex AHSN’s Director of Insight (chair), Associate Director of Insight (evaluation lead), program manager, and data analyst; the CHOICE chief investigator and PM; a strategic advisor from Consilium Partners Ltd; the Director of R-Outcomes Ltd; the RUBIS.Qi evaluation lead (coaching organization provided by the funder); and a patient. The CHOICE team does not take decisions on the evaluation but collaborate and provide input as required. The EAG also provides a forum for reflecting on the findings of the evaluation during the course of the project and enable improvements in the scaling up of CHOICE via formative learning.

#### Industry Advisory Group

The industry advisory group was formed to ensure 2-way dialog with the device manufacturers of cochlear implants. This stakeholder group is purposefully separate from the SG so that CHOICE continues its ethos of being patient centric, charity funded, and agnostic of individual industry parties. The industry advisory group meets every 6 months and comprises the chief investigator and PM and 1 representative from each of the 4 cochlear implant companies: Advanced Bionics UK Ltd, Cochlear Europe Ltd, MED-EL UK Ltd, and Oticon Medical Ltd.

We have not established an independent data monitoring committee, as this is not a clinical trial, and it is not a requirement of the funder. The funder may observe, monitor, and inspect the delivery of the project and reserves the right to externally evaluate any aspect of the project and its outputs. The funder may need to allow members of The Health Foundation Research Directorate to inspect anonymized records and data, including recordings and transcripts of interviews with patients and others.

#### Patient and Public Involvement

The project team has a strong commitment to patient and public involvement, and a member of the project team is a service user (CR). Local and national publicity (through the website, Twitter, presentations to National Cochlear Implant Users’ Association, newsletter articles, letters, emails, and Yahoo group) has already invited help in designing the project. Several people using cochlear implants have trialed the CHOICE website and the hearing check before its release and have provided feedback in writing and focus groups.

A risk assessment was approved by the University of Southampton Faculty of Engineering and the Environment on May 15, 2018 (FEERA 15927).

### Data Management

The data will be managed according to the University of Southampton Research Data Management Policy. The study’s data management plan and data protection impact assessment are available upon request. Deidentified data will be kept at the University of Southampton for at least 10 years. If patients decide to stop using CHOICE, we will keep the information we have collected thus far unless participants request that it be deleted. It will not be possible to delete data if they have already been anonymized. Individual cochlear implant centers will retain their own clinical patient data according to local policies.

Regarding evaluation data, only deidentified data will be provided to the independent evaluator, who will handle and store this in accordance with the agreements that are put in place at each site. Wessex AHSN will ensure that the data are handled in line with NHS standards, including data collection, code of practice, and information governance. The AHSN computer network is a private cloud-based system compliant with ISO 27001 and approved under the NHS Information Governance Toolkit. The cloud servers are based in the United Kingdom.

The retention schedule for data collected by Wessex AHSN is as follows:

Audio recordings will be kept until the publication of the evaluation report (July 2021) and then destroyed.All other data, including transcriptions of the audio recordings, will be kept until 12 months after publication of the evaluation report (July 2022) and then securely transferred to the University of Southampton (under the control of the chief investigator) to be retained until 10 years after the study conclusion.

### Ethics and Dissemination

Ethical approval was received in November 2018 from the South Central–Hampshire A research ethics committee (REC reference 18/SC/0658; IRAS project ID 242575), Health Research Authority, and Health and Care Research Wales.

#### Confidentiality

Personal and sensitive personal data will be entered into the web app by the patient. The patient will consent to data sharing. The data will be encrypted before transfer. At the close of the project or before, the data will be deidentified (personal data removed). We cannot guarantee anonymity as adults with cochlear implants are still rare in the general population (approximately 0.01% of the UK population or approximately 1 in 10,000 people).

Interviews (with staff and patients) will be audio recorded using an encrypted dictaphone and transcribed. Any used names will be removed after transcription. Data relating to individuals will not be linked together; that is, individual interviews and individual R-Outcomes data will not be linked. The findings will be linked through a synthesis process at the aggregate level. Safety monitoring and reporting of adverse events will occur according to the requirements of the local and national ethics committees, with full support from the sponsor.

#### Dissemination

The results will be presented locally, nationally, and internationally. Dissemination will include but not be limited to peer-reviewed publications both on the web and in print, conference and meeting presentations, posters, newsletter articles, website reports, and social media. To inform people with cochlear implants of the results, information will be sent to the National Cochlear Implant Users’ Association and other patient groups and the University of Southampton Auditory Implant Service patient newsletter. We have budgeted for our academic publication of clinical results to be gold open access. The results of this evaluation will be published in a report by Wessex AHSN.

## Results

As of July 2021, the trial is closed, and all data collection is complete. The evaluation report is expected to be published in December 2021, and the research data have not yet been analyzed.

## Discussion

### Limitations

A total of 7 sites agreed to participate in the implementation and evaluation of CHOICE. These sites are mostly larger adult cochlear implant centers in England. Sites were self-selected: those participating were the centers that expressed interest in taking part. This means that it is unlikely that these centers are representative of all UK adult cochlear implant centers; they are likely to be more willing to innovate. Given that data collection will commence as soon as centers and patients join CHOICE, there will be variable periods of follow-up.

We expect significant effect modification in subgroups (eg, by age, gender, cochlear implant center, and other demographic factors). Assessing and reporting effect modifications may help identify a subset of patients who would not benefit from remote care. We attempted to control for confounding factors by collecting the demographic and digital readiness data. However, it is possible that there are confounders that remain unaccounted for; for example, we will not collect data on mental health and social support or the impact of the COVID-19 pandemic. It is likely that the concurrent COVID-19 pandemic will be the largest confounding factor in the data. In addition, the coincidental launch of a manufacturer-led remote care pathway (Cochlear Remote Check) for patients with some devices is likely to confound the results. The nature of recruitment for this study (cochlear implant center choosing to be involved and patient choosing to take part) means that there is likely to be a significant bias. Patients who choose to take part in a trial of remote care may not be representative of the broader population of people with cochlear implants. As recruitment is performed via patient and clinic choice, it is not valid to have a control group of people who do not follow a remote care pathway.

We are aiming for 6 months of follow-up data. This may be insufficient to highlight the benefits and limitations of remote care, especially in the climate of change because of the COVID-19 pandemic. In addition, as patients are encouraged to register for CHOICE at any point, there may only be a very short experience of using CHOICE by the end of data collection for many people.

The PAM may not be very sensitive to changes in the empowerment of people using cochlear implants because of its medical perspective. Given that this is the first time there has been a large-scale rollout of a remote care model for cochlear implants, we do not know how many people will participate. Low patient numbers and dropouts are likely to affect the quality of the results, although reporting them will provide important information on the success of the implementation. Patients who discontinue the use of CHOICE will be asked to provide a reason for their withdrawal.

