We previously designed and implemented a remote care pathway for adults with cochlear implants to enable them to perform some of the follow-up tasks themselves at home. We ran a 6-month clinical trial with 60 people randomized to either a telemedicine remote care pathway or a control group who followed their usual appointment schedule [10]. The main outcome evaluated was patient empowerment, which has been shown to be strongly linked to better outcomes in people with long-term conditions. We found that only the remote care group had a significant increase in their cochlear implant empowerment after using remote care tools. The quality of life remained unchanged in the 2 groups. The hearing check results in the clinic improved in the remote care group, although they did not notice a change. However, the control group felt that their hearing had become slightly worse. This may suggest that the remote care group was better able to take action to keep their hearing stable during the trial, or, perhaps, the control group felt they were missing out on a desirable opportunity to take a more active role in their hearing health care.

Discontinuing routine appointments and attending the clinic only when there is a clinical need may provide the following benefits for patients using cochlear implants:

More stable hearing (problems identified and resolved quicker)Better hearing (ability to fine-tune when away from the clinic)Convenience of not traveling for routine appointmentsReduction of travel costs and time, time off work, and disruption to family lifeIncreased confidence in managing one’s own hearingGreater equality in service delivery (same level of service regardless of distance from the clinic)

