## Methods

### Project Design and Setting

This is a prospective, interventional, multisite, quality improvement project led and sponsored by the University of Southampton. All research measures will be self-administered on the web or by a paper questionnaire at the patient’s home or other locations of their choice. The staff will complete the measures at work or at a location of their choice. Data collection began when the first site opened on June 11, 2019**,** and continued until January 31, 2021. Clinics will join the study when appropriate local approvals are obtained; therefore, it is likely that the follow-up at each clinic will be for different durations.

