##### Services Outcomes: Quantitative Measures

Local service-level activity data will be collected at all sites with a view to assessing resource use and the workforce (Multimedia Appendix 1). We aim to obtain data from all clinic patients to maximize the sample size. A cohort of patients will also be identified for comparison. This will comprise patients registered with clinics but who have not yet been offered the new care model. We will look at the aggregated clinical activity before and after the introduction of the tool (eg, numbers of outpatient appointments and DNAs in the inclusion group). There will not be a control group of patients undergoing the same measures as the intervention group. We will also analyze the centers’ previously collected service-level data to evaluate the current pathway.

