#### Quantitative

Descriptive statistics and graphs will be used to present the data. Data will be displayed visually wherever possible to facilitate sharing with various stakeholders. The significance value will be set at *P*=.05, including Bonferroni corrections for multiple comparisons where appropriate. All repeated-measures data will be compared at baseline and follow-up using analysis of variance to examine any changes in empowerment, hearing, and quality of life in the participants. Surveys will be analyzed at the baseline and follow-up time points using inferential statistical analyses. The choices of participants in the DCE will be subjected to conditional logit model analysis using the *survival* package of the R programming language.

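### Subgroup differences in single-arm before-after change cannot show which patients would not benefit from remote care, because effect and background change are not separable

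*Protocol article*

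**What the plan says.** Under Limitations, the protocol article states: "We expect significant effect modification in subgroups (eg, by age, gender, cochlear implant center, and other demographic factors" and continues: "Assessing and reporting effect modifications may help identify a subset of patients who would not benefit from remote care". The same section says that, given how patients and clinics are recruited, "it is not valid to have a control group of people who do not follow a remote care pathway".

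Under Services Outcomes: Quantitative Measures it says: "There will not be a control group of patients undergoing the same measures as the intervention group". The comparison cohort announced there ("A cohort of patients will also be identified for comparison") belongs to the service-level activity data, such as appointment counts. Table 1 lists the empowerment and quality-of-life questionnaires at registration and at 6 months or project end if that is earlier, and takes all home hearing check results. All of these come from patients on CHOICE.

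The analysis, under Data Analysis, Quantitative, is: "All repeated-measures data will be compared at baseline and follow-up using analysis of variance to examine any changes in empowerment, hearing, and quality of life". No subgroup test or decision rule is given there.

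**The concern.** Effect modification and failure to benefit are causal terms. They compare what happens to a kind of patient with CHOICE and without it. The design records only the first. A subgroup that would have declined anyway can show no gain even though CHOICE slowed its decline, and a subgroup that gains nothing can look improved because it was improving for other reasons.

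The statement concerns who gains from a pathway that, according to the Participants overview, may later be offered to all sites. A wrong label in either direction could carry into that rollout. Collecting demographic and digital readiness data, as planned, does not supply the missing quantity, which is each subgroup's change without CHOICE.

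**Working it through.** **No figure to reproduce.** The article gives no power, error rate or sample size for subgroups, and the Proposed Sample Size section says no calculation was done. The check is therefore one of identification, followed by an illustration on assumed values.

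**Step 1: what a subgroup contrast estimates.** In one arm, for subgroup g:

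mean change(g) = effect(g) + background change(g)

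so for subgroups A and B:

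difference in change = [effect(A) − effect(B)] + [background(A) − background(B)]

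The second bracket must be zero, or known, before the contrast can be read as effect modification. A concurrent control group on the same measures would estimate background(g); the article rules one out. If only patients with follow-up are analyzed, a selection term is added for each subgroup.

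**Step 2: reasons in the article to doubt that the second bracket is zero.**
- *Center timing.* Clinics join as approvals arrive, and "it is likely that the follow-up at each clinic will be for different durations". Data collection ended on January 31, 2021, so a patient registering after July 31, 2020 has less than 6 months. A late-joining center has more such patients. Center, a named subgroup factor, is thus mixed with calendar period and exposure.
- *Pandemic.* Limitations expects it to be the largest confounder and says its impact is not recorded.
- *Competing pathway.* Limitations notes a manufacturer's remote pathway available only for some devices, so it does not touch all patients alike.
- *Dropout.* The Missing Data section expects data mostly missing not at random, because those who find CHOICE less helpful leave. The patients being sought are the likeliest to lack follow-up.

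**Step 3: illustration.** Assumptions, none from the article except the ceiling of about 1700 patients: two equal subgroups of n = N/2, equal true benefit, background change differing by d (in baseline SDs), two-sided 5% test of the difference in change. With baseline/follow-up correlation r:

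SD of change s = √(2(1 − r)); SE = s√(2/n); rejection = Φ(d/SE − 1.96) + Φ(−d/SE − 1.96)

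Worked case: r = 0.5, so s = 1; N = 1700, n = 850; SE = √(2/850) = 0.0485; d = 0.1; d/SE = 2.06; rejection = 54%.

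| r (s) | d | N = 400 | N = 850 | N = 1700 |
|---|---|---|---|---|
| either | 0 | 5% | 5% | 5% |
| 0.5 (1.000) | 0.1 | 17% | 31% | 54% |
| 0.5 (1.000) | 0.2 | 52% | 83% | 98.5% |
| 0.7 (0.775) | 0.1 | 25% | 47% | 76% |
| 0.7 (0.775) | 0.2 | 73% | 96% | >99.9% |

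**Step 4: both kinds of error (s = 1).**
- *False flag.* Effect 0.3 in A and B, background 0 in A and −0.3 in B. B's mean change is 0.3 − 0.3 = 0, so it looks like a group that does not benefit. The contrast is significant in 56% of studies at N = 200 and 85% at N = 400.
- *False clear.* Effect 0.3 in A and 0 in B, background 0 in A and +0.3 in B. The contrast is 0.3 − 0.3 = 0, so rejection stays at 5% at every N, while B shows a significant improvement in 85% of studies at N = 200 and 99% at N = 400.

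More patients make the false flag more certain. The planned Bonferroni correction limits chance findings across many tests; it does not remove this bias.

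**The case against.** The strongest reply is that the sentence is a hedged remark in a Limitations section, that the paragraph around it admits unmeasured confounders, the pandemic, the competing pathway and the lack of a control group, and that the same weakness affects the main before-after result. This is largely fair. What survives is that the caveats are not attached to the subgroup inference, which is offered as something useful. The hedge conveys doubt about whether a subset will be found, not that these data cannot identify one.

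Four stronger readings are tempting, and the article does not support them.
- *That a subgroup-by-time test is planned and its result decides who stays on the pathway.* No such test or rule is stated. The test used above is inferred from the repeated-measures analysis of variance. The Recruitment section leaves pathway choice to shared decision-making, with easy transfer to clinic-based care.
- *That the earlier trial shows unequal background change.* It reports that "the control group felt that their hearing had become slightly worse", but for that group as a whole, not by subgroup, and the article also suggests those patients may have felt they were missing out.
- *That older patients or one gender will be mislabeled.* The timing argument applies to center and the competing pathway to device; nothing specific to age or gender is documented.
- *That the rejection rates forecast this study.* They rest on assumed background differences, correlations and subgroup sizes, and 1700 is an expected recruitment ceiling, not a number with follow-up.

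**Conclusion.** The point stands in limited form. With patient outcomes from a single arm, subgroup differences in change do not estimate effect modification, and lack of benefit in a subgroup is not identified. That conclusion follows from the design and needs no numerical assumption.

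The size does need assumptions. For a background difference of 0.1 to 0.2 SD and r of 0.5 to 0.7, the chance of a misleading significant contrast runs from 17% to 73% at 400 patients and from 54% to over 99.9% at 1700, against a nominal 5%. If background change were equal across subgroups and dropout did not select differently, there would be no distortion; the article gives reasons to doubt this but no magnitude. The fault lies in a stated inference, not in a wrong calculation or a faulty allocation rule, and it is cheap to correct.

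**What to change.** In Limitations, replace the sentence on identifying patients who would not benefit with wording such as: *Differences between subgroups in change from baseline will be reported with confidence intervals as exploratory descriptions of change while on CHOICE. They are not estimates of effect modification and not evidence that a subgroup does not benefit. The confounding and missing-data caveats given in this article apply to them.*

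The preceding sentence, which expects effect modification, should be reworded to expect differences in change.

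Adjust center comparisons for registration month and time on CHOICE (registration to follow-up). This reduces the timing problem but does not make the contrast causal.

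To describe whom the pathway does not suit, use withdrawal reasons, use data and interviews, all already collected. Hearing deterioration flags can be reported, but they rest on comparison with a baseline check and have the same missing counterfactual.

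Cost: a few sentences and two covariates available from registration and follow-up dates, with no new data. The downside is that the report gives up a statistical claim about which subgroup does not benefit.

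### Demographics and digital readiness cannot remove confounding of the before-after change in question 2; the pandemic, named as the likely largest confounder, is pooled over although measurement dates could partly separate it

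*Protocol article*

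**What the plan says.** The research question (Primary Research Questions, question 2) is whether the pathway increases empowerment with no detriment to hearing or quality of life. Data Analysis, Quantitative, sets the method: "All repeated-measures data will be compared at baseline and follow-up using analysis of variance to examine any changes in empowerment, hearing, and quality of life". No covariate, calendar term or period stratum is named there. Services Outcomes states: "There will not be a control group of patients undergoing the same measures as the intervention group".

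On confounding, Limitations says "We attempted to control for confounding factors by collecting the demographic and digital readiness data". It then concedes that confounders may remain, for example that "we will not collect data on mental health and social support or the impact of the COVID-19 pandemic". It adds: "It is likely that the concurrent COVID-19 pandemic will be the largest confounding factor in the data". It names a second time-related threat: "the coincidental launch of a manufacturer-led remote care pathway (Cochlear Remote Check) for patients with some devices is likely to confound the results". Just before this, the same section lists age, gender and centre as expected effect modifiers.

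On timing, Table 1 places the empowerment and quality-of-life questionnaires at registration and at 6 months after it, or at project end if sooner. Recruitment and data collection ran from June 11, 2019 to January 31, 2021. Digital readiness is part of R-Outcomes, which is repeated every 6 months. The Results section says the research data had not yet been analyzed.

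**The concern.** The control that the protocol offers does not match the contrast that it plans. When each patient is compared with themselves, a trait that does not change between the two measurements drops out of the mean change, whether or not it was recorded. Adjusting for it cannot remove bias from something that happened between the two dates. Digital readiness measured again at follow-up does not help either, because using CHOICE may itself have altered it.

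The threats to the mean change are therefore time-related. The protocol names two, the pandemic and the manufacturer's remote pathway, and the stated analysis separates neither. Followed as written, it gives one pooled change that mixes patients measured wholly before, across and wholly during the pandemic. Any pandemic shift in empowerment, quality of life or perceived hearing is carried into the figure that answers question 2.

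**Working it through.** **1. Which terms survive in a within-patient change.** Write each score as a fixed part b·X (age, gender, baseline digital readiness), plus a calendar effect g(t), plus noise, with the true change τ added at follow-up. Then

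change = τ + [g(t₁) − g(t₀)] + noise.

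The term b·X cancels; the calendar term does not. If the pandemic effect is a single step δ, the pooled mean is τ + δ × (share straddling the onset).

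**2. How many patients straddle.** Inputs from the protocol: registration from June 11, 2019 to January 31, 2021, and follow-up at 6 months (taken as 183 days) or project end. Assumptions: uniform registration, and onset on March 16, 2020, because the protocol gives no onset date.

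- Registration days, both ends counted: 601. Days allowing a full 6 months: 601 − 183 = 418. (Dropping one end day gives 417; the shares are the same to the nearest percent.)
- Onset falls 279 days after the first registration day.
- Both measurements before: 279 − 183 = 96 days.
- Straddling: 183 days.
- Both after, full 6 months: 418 − 279 = 139 days.
- Both after, follow-up cut short by project end: 601 − 418 = 183 days.

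| Stratum | Share of 601 days | Share of 418 days |
|---|---|---|
| Both before | 96/601 = 16% | 96/418 = 23% |
| Straddling | 183/601 = 30% | 183/418 = 44% |
| Both after | (139 + 183)/601 = 54% | 139/418 = 33% |

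Moving the assumed onset from February 1 to April 1, 2020 moves the both-before share of the 601 days from 8.7% (52 days) to 18.6% (112 days). The straddling share stays at 30.4%.

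**3. What adjustment does.** An illustrative simulation used 200,000 patients, uniform registration, onset on March 23, 2020, a true change of 0.20 and a pandemic step of −0.30. All effect sizes are assumed. By the formula, the pooled mean should be 0.20 − 0.30 × 183/601 = 0.109.

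| Estimate of mean change (truth 0.20) | Step effect | Effect building up over time |
|---|---|---|
| Crude pooled | 0.111 | 0.043 |
| Adjusted for baseline age and digital readiness | 0.111 | not run |
| With a period term from dates | 0.208 | 0.045 |
| Both before | 0.204 | 0.204 |
| Straddling | −0.108 | 0.039 |
| Both after | 0.209 | −0.007 |

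The baseline covariates leave the bias where it was. Dates recover the truth if the effect is a step. If it builds up, only the both-before stratum is unbiased.

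**4. Where the covariates do matter.** In the same simulation, letting digital readiness modify the change and also drive dropout gave a mean change of 0.206 in completers against 0.112 in the full cohort. These data are worth collecting, but for selection and effect modification.

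**The case against.** The strongest reply is that the protocol hides nothing. It says only that control was attempted, admits that confounders remain and calls the pandemic the largest. A reader might infer that the article claims confounding was controlled, or that it credits pandemic shifts to CHOICE. The text supports neither reading; Limitations warns against both.

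Second, a reader might infer that demographics can never confound here. That is too broad. Services Outcomes says "A cohort of patients will also be identified for comparison", and the discrete choice experiment preferences are to be correlated with outcomes. Both compare different patients, so such traits can confound them. The point holds only for fixed traits in the before-after change.

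Third, dates do not isolate the pandemic. There is no control group on the same measures, the clean stratum is small, and a period term fails if the effect evolves. Comparing early registrants' follow-up with later registrants' baseline does not escape this: it is a between-patient comparison, open to selection and to the dropout that Missing Data expects to be mostly not at random.

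Fourth, a condensed article may leave covariates and sensitivity analyses to a fuller document. That excuses silence on detail. It does not correct a sentence that gives the collected covariates a role they cannot play in the stated analysis.

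One might also argue that ignoring centre makes standard errors too small. The protocol gives no within-centre correlation from which to size this, and it already names centre as an expected effect modifier, so no claim is made here.

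**Conclusion.** The point stands in limited form. For question 2, collecting demographics and baseline digital readiness does not address confounding of the mean within-patient change. The time-related threats that do confound it are named but left pooled, although each planned measurement is tied to the registration date.

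On the stated assumptions, about 30% of registration days (44% of those allowing 6 months) yield pairs that straddle the onset. Only about 16% (23%) yield pairs wholly before it, and probably fewer in practice, because clinics joined as approvals arrived. The direction and size of any actual pandemic effect are unknown; the simulated values only show the mechanism. Because the protocol discloses the pandemic openly, the defect is a mismatch between stated control and stated analysis. It is not a misstatement that confounding was resolved. It is worth correcting before the data are analyzed.

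**What to change.** 1. **Add a prespecified sensitivity analysis.** Using registration and questionnaire dates, report the baseline to follow-up change separately for patients with both measurements before, straddling, and both after the start of pandemic restrictions. Fix the cut-off date in advance, and state whether the pooled result is consistent across the strata.
2. **State how the strata will be read.** The both-before stratum is the cleanest but small. The both-after stratum may still carry an evolving pandemic effect, and many of its patients will have less than 6 months of follow-up.
3. **Reword Limitations.** Describe demographic and digital readiness data as addressing effect modification and selection (including dropout), and as possible adjusters in the between-patient comparisons. Describe the question 2 result as change among users, not as an effect of CHOICE.
4. **Optional.** If early registrants' follow-up is compared with later registrants' baseline, adjust for demographics and baseline digital readiness and label the comparison exploratory.

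The cost is analysis time and wording; no new data are needed provided completion dates are held with the questionnaires. The downside is less precise stratum estimates and a pandemic effect that is only partly separated.
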